### Post-operative rehabilitation

Post-operative rehabilitation will follow routine clinical care at NNUH and Spire Norwich [24, 25]. While an inpatient, participants will be seen by a physiotherapist for routine care at least twice daily to progress on a tailored gait re-education and exercise programme during their hospital admission. This will be recorded in an in-patient hospital rehabilitation log. Once safe for discharge, patients will be asked to continue a home exercise programme and gait re-education. This will consist of daily (advised) knee-flexion range-of-motion exercises and quadriceps strengthening.

At week 4 post-operatively, all participants will attend an exercise-group-based intervention delivered by a qualified physiotherapist and a physiotherapy assistant. These sessions will be used to increase participant’s knee range of motion, strength and overall confidence to undertake more strenuous exercises. Participants will attend this class weekly for two to six sessions depending on their need. All rehabilitation interventions will be recorded in a post-discharge rehabilitation log. Participants will be encouraged to continue their exercises which are prescribed within the group as part of a home-exercise programme.

No additional ancillary or post-trial care will be provided (in the absence of AEs) to trial participants.

### Outcomes

The schedule of enrolment, interventions and assessment is shown in Table 2. The PROMs will be administered by research nurses apart from the week-1 follow-up telephone call undertaken by the research associate performing the qualitative interview. The CT scans will be performed at the NNUH by research radiographers and reported by a consultant radiologist. The biomechanical assessments and qualitative interviews will be performed at the MoveExLab at the UEA. Participants who were unable to attend an assessment appointments were provided with an alternative appointment. If participants were unable to attend any alternative assessment appointments, PROMs data was collected during a telephone call to promotion participant retention and follow-up.

**Table 2 Tab2:**
[figure not shown]
Schedule of enrolment, interventions and assessments

*subset of 30 patient; *CT* computerised tomography, *HADS* Hospital Anxiety and Depression Score, *MVIC maximum voluntary* isometric contraction, *OKS* Oxford Knee Score, *OKS-APQ* Oxford Knee Score Activity and Participation Questionnaire, *Pre-Op* pre-operative, *Post-Op* post-operative, *ROM* range of motion, *UCLA* University of California Los Angeles

### Primary outcome

The OKS [16] will be used to assess patient-reported functional status at 6 months post surgery.

#### Secondary outcomes: Patient-Reported Outcome Measures

The Oxford Knee Score (OKS) [16] – Activity and Participation Questionnaire (OKS-APQ), [26] EuroQol 5 dimensions, 5 levels health survey (EQ-5D-5 L) [27], UCLA Activity Score [28], Hospital Anxiety and Depression Score (HADS) [29], Forgotten Joint Score (FJS) [30], and 2-Item Pain Self-Efficacy Questionnaire [31].

#### Secondary outcomes: clinical efficacy outcomes

Clinical efficacy will be evaluated by:
Surgical-related parameters: need for revision surgery; length of hospital stay and change in pain medication will be collected during in-patient stay and at all the follow-up time pointsPerformance-related parameters: knee flexion and extension ranges of movement, measured at 6 to 8 weeks and 6 months post-operatively by the research associate in the MoveExLab (and by the research physiotherapist at baseline as part of routine care); timed-up-and-go (TUG) [32] and timed 6-minute walk test [33] recorded at the 6–8 week and 6-month time points by the research associate in the MoveExLab

#### Secondary outcomes: clinical safety outcomes

Complications related to the surgery (e.g. anaesthesia-related problems, bleeding, morbidities) will be collected from a notes review, prior to discharge, post-discharge, rehabilitation and follow-up. Additionally, at each visit, participants will be asked whether they have received additional treatment since their surgery/previous visit and what that consisted of.

#### Secondary outcomes: biomechanical outcomes

All biomechanical measures will be collected in the MoveExLab by the research associate. Three-dimensional motion capture using eight cameras (Vicon Motion System, Oxford, UK), three built in force plates (Bertec Corporation, Columbus, OH, USA) and surface electromyography (EMG) (Delsys, Natick, MA, USA). Participants will be unshod and asked to walk at their self-selected speed. A minimum of three heel strikes from each foot will be used to construct an average.
Overground walking: unshod and walking at self-selected speed:
Spatiotemporal parameters; speed, cadence, step-length, stride-length and symmetryKinematics of bilateral hip, knee and ankle jointsKinetics: moments of bilateral hip, knee and ankle joints and ground reaction forces during the stance phaseEMG parameters: recruitment patterns of quadriceps: rectus femoris, vastus medialis and vastus lateralis, hamstrings: semitendinosus, biceps femoris, tibialis anterior, medial and lateral gastrocnemiusStair ascent and descent:
Spatiotemporal parameters; speed, cadence, symmetryKinematics of bilateral hip, knee and ankle jointsKinetics: moments of bilateral hip, knee and ankle joints and ground reaction forces from the bottom step

Static balance measures will be completed on a single, in-built force plate (Bertec Corporation, Columbus, OH, USA). Participants will be instructed to stand with their feet shoulder-width apart for double stance with their eyes closed and then open for 10 s. Three attempts will be recorded. Participants will then be instructed to stand on one leg in the centre of the force plate with their hands on their hips with their eyes open and closed for 10 s. Each limb will be tested. Three trials of 10 s will be recorded. The time will be stopped if the participant places the other foot on the floor. Each participant will be given six attempts at each position.
3.Static balance; measures of centre of pressure (CoP) from single- and double-leg standing
Anterior-posterior (AP), medial-lateral (ML) and CoP path lengthAP, ML and CoP velocityAP, ML and CoP range and standard deviation (SD)4.Time-to-boundary (TTB) [34]
TTB minimum, mean and SD5.Modified Star Excursion Balance Test (mSEBT) [35]
Anterior, posteromedial and posterolateral distance (millimetres) on both limbs

#### Secondary outcomes: radiological outcomes

##### Radiographs

Pre-operative and post-operative conventional semi-flexed AP and lateral radiographs of the knee will be acquired.

##### Computerised tomography

A rotational-profile CT protocol will be acquired at the NNUH Radiology Department under standard operating procedure.

This will consist of three separate axial acquisitions through the femoral necks, knees and ankles reconstructed on bone and soft-tissue algorithms. The images through the knee will be split into two acquisitions according to the Berger protocol [36]. The pre-operative CT will be performed in the time after consent for the study and before TKR. The post-operative CT is not time sensitive and will be performed any time following surgery.

Two independent observers, radiologists under direct supervision of a senior musculoskeletal radiologist, will obtain the following measurements from the CT. In the case of disagreement between the two independent observers, through discussion, the senior musculoskeletal radiologist will act as adjudicator to ensure that agreement is met. Measurements will include:

##### Pre-operative

Femoral ante-torsion (degrees)Tibial tubercle-trochlear groove distance (TT-TG) (millimetres)Tibial torsion (degrees)

##### Post-operative

Femoral ante-torsion (degrees)Femoral-component version (degrees)Tibial-component version (degrees)Tibial torsion (degrees)

In the event of an incidental finding being reported, the clinical chief investigator will organise the necessary clinical follow-up which may include referral to an appropriate clinician and the organisation of further investigations.

#### Secondary outcomes: qualitative study

Interviews will be completed either via a telephone call or face-to-face by the research associate. This flexibility was adopted to promote participant retention and complete follow-up. These interviews will be audio-recorded and transcribed for analysis.

All TKR participants will be invited to take part in an interview and complete a self-efficacy questionnaire and the HADS at baseline and a telephone call interview at the 7 days (± 2 days) surgery.

Two additional post-surgery interviews will be carried out with a purposive sample of participants (*n* = 30), drawn equally from the intervention and control groups. Sampling decisions will be based on the following factors: age; sex; ethnicity; socioeconomic status; OKS; self-efficacy; expectations, mood and symptom management (as ascertained from inspection of baseline interviews).

The aims of the interviews are to gain in-depth understanding of patient perspectives on important variables known to affect outcomes of TKR surgery [4, 37–39]. Specific themes will be:
To explore patients’ expectations of and hopes for surgery (pre-operative only)To explore patients’ experiences and perspectives on: mood, pain and function – everyday mobility, participation in work, social roles and activities; surgery and post-operative clinical management; rehabilitation and recovery, and social support

All surgeons will be invited to consent to a face-to-face interview after the last participant’s surgery to explore their perspective on using each prostheses and their overall experience of surgery.

## Methods: assignment of interventions

### Allocation

An interactive web-randomisation system will be used by a member of the research team who is not blinded to the intervention. Participants will be randomly assigned to either control or experimental group with a 1:1 allocation as per a computer-generated randomisation schedule. Randomisation will occur after the completion of all baseline tests. This will take place 4 days (± 3 days) prior to the operation to allow the correct TKR to be made available. Randomisation will be stratified by: (1) site (i.e. hospital where surgery is to take place); and (2) age (< 60 years = younger; equal or ≥ 60 years = older) [40, 41].

### Blinding (masking)

It is not possible to blind the surgeon to the trial intervention. However, the participants, the physiotherapists and all staff involved in assessing outcomes will be blinded. Processes will be in place to maintain blinding. These will include concealment in a sealed envelope of the surgery notes mentioning the prosthesis implanted in the patient file.

In the unlikely event of a research nurse accidentally becoming unmasked, the contacts, assessments and data entry for that participant will be undertaken by another member of the research team for the remaining period of trial participation for that participant. Accidental unmasking will be logged and monitored to ensure that the appropriate steps are taken to prevent a re-occurrence.

The clinical staff providing usual care will also be blinded. The decision to unmask a case will be made when knowledge of an individual’s allocated treatment is required to enable treatment of a serious adverse event (SAE) which is likely to be caused by the type of device implanted.

Where possible, requests for emergency unmasking of individuals will be made via the trial manager in agreement with the clinical chief investigator. However, in circumstances where there is insufficient time to make this request or for agreement to be sought, the treating clinician can make the decision to unmask immediately. This can be done via the trial database.

## Methods: data management and analysis

### Data management

Each participant will be given a unique trial Participant Identification Number (PIN). Data will be entered under the participant’s PIN number onto the central database stored on the servers based at NCTU. Access to the database will be via unique, individually assigned (i.e. not generic) usernames and passwords, and only accessible to members of the CAPAbility trial team at NCTU, and external regulators if requested. The servers are protected by firewalls and are patched and maintained according to best practice. The physical location of the servers is protected physically and environmentally in accordance with UEA’s General Information Security Policy 3 (GISP3: Physical and environmental security).

The database and associated code have been developed by NCTU Data Management, in conjunction with the CAPAbility trial team. The database software provides a number of features to help maintain data quality, including; maintaining an audit trail, allowing custom validations on all data, allowing users to raise data-query requests and search facilities to identify validation failure/missing data. After completion of the trial, the database will be retained on the servers of NCTU for on-going analysis of secondary outcomes.

The identification, screening and enrolment logs, linking participant identifiable data to the pseudoanonymised PIN, will be held locally by the trial site. This will either be held in written form in a locked filing cabinet or electronically in password-protected form on hospital computers. After completion of the trial, the identification, screening and enrolment logs will be stored securely by the sites for 15 years unless otherwise advised by NCTU. The consent form will explain that if a participant wishes to withdraw from the study the data acquired prior to that point will be retained. Reason for withdrawal will be recorded, if given, as will loss to follow-up.

### Statistical analysis

A full Statistical Analysis Plan (SAP) will be developed between the trial statistician and chief investigators and agreed with the trial’s Governance Committees. All analysis will be based on the intention-to-treat principle in which all participants will be analysed according to the group to which they were allocated, regardless of compliance.

Baseline factors will be summarised by group. All continuous variables will be summarised by the mean and SD, or if appropriate, the median and interquartile range. Categorical variables will be summarised with the number and percentage, in each category.

The primary comparison for OKS will be made using a general linear model with the stratification factors included as fixed effects. The difference between arms will be summarised using the mean difference, with 95% confidence intervals presented. A similar analysis will be undertaken for all other outcome measures.

For the temporal gait parameters and kinematic outcomes, each participant’s ‘closeness’ to age-matched normative data will be calculated. This will then be compared between groups using a general linear model with the stratification factors included as fixed effects. This data will also be presented graphically via scatter and distributional graphs to describe the deviations from the normative data.

For all the measures of movement listed, a general linear model with the stratification factors included as fixed-effects will be used to assess for between-group differences. If appropriate, adjusted analyses will be undertaken by including baseline factors and fixed effects in the above models.

### Assumptions and sensitivity analysis

All the assumptions will be checked via distribution graphs and tests. If the assumptions are not valid, transformation will be considered. If none are found, a non-parametric approach will be used. The pattern of missing or incomplete data will be assessed. If appropriate, missing data will be imputed. The baseline comparability of the groups will be assessed. If appropriate, any factor found to be imbalanced and important, will be adjusted for in the analysis.

Exploratory subgroup analysis will be undertaken by including an interaction in the model to assess whether the effectiveness of the prosthesis is dependent on age or gender.

All analyses will be conducted using Stata and the full SAP will be produced, and approved, before any comparative analysis is undertaken.

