### Sample size

Eighty patients will be recruited onto this superiority trial. The sample size has been calculated from the Oxford Knee Score (OKS) [16]. The OKS ranges from a score of 12 to 60, with 12 being the best outcome. The minimally important clinical difference for OKS is 5 [17, 18] and a standard deviation of 7.4 [19]. For an 80% power, and an assumed dropout rate of 10%, 80 participants will be randomised to one of the two groups.

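### Adjustment beyond site and age depends on observed baseline imbalance, and the primary model does not name baseline OKS

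*Protocol article*

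**What the plan says.** All references are to the protocol article.

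- **Statistical analysis**, primary model: "The primary comparison for OKS will be made using a general linear model with the stratification factors included as fixed effects". Under Allocation these factors are site and age, the latter split at 60 years: "Randomisation will be stratified by: (1) site (i.e. hospital where surgery is to take place); and (2) age". Baseline OKS is not named.
- **Statistical analysis**, further models: "If appropriate, adjusted analyses will be undertaken by including baseline factors and fixed effects in the above models". The baseline factors are not listed. The same section describes the baseline table as descriptive summaries by group.
- **Assumptions and sensitivity analysis**: "The baseline comparability of the groups will be assessed". Then, where appropriate, "any factor found to be imbalanced and important, will be adjusted for in the analysis". No measure of imbalance, threshold, list of factors or definition of importance is given.
- **Assumptions and sensitivity analysis**, closing paragraph: the full SAP is to be approved ahead of any comparison between the arms.
- **Sample size**: a difference of 5 OKS points, a standard deviation of 7.4, and "For an 80% power, and an assumed dropout rate of 10%, 80 participants will be randomised to one of the two groups".

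**The concern.** Allocation is random, so any baseline difference between the arms is due to chance. Its observed size says nothing about whether a covariate is worth adjusting for. What matters is how strongly the covariate predicts the outcome, and that can be judged before any data are seen. Requiring a factor to be both imbalanced and important drops a strong predictor in every trial where it happens to balance, although adjusting for it would still narrow the confidence interval.

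This bears directly on baseline OKS. The principal aim is stated as change in patient-reported scores from before surgery to 6 months, and randomisation follows the baseline tests, so the value will be available. Yet it can enter the OKS model only through two discretionary routes: the optional adjusted analyses, or the imbalance rule.

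Two things are at stake. The precision that baseline OKS could give is not secured. And a reader cannot tell whether a factor brought in by the imbalance rule changes the primary estimate or only a supporting one.

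**Working it through.** **Inputs.** Difference 5, SD 7.4, power 80%, dropout 10%, 80 randomised (Sample size); 1:1 allocation (Allocation). Two-sided 5% significance is assumed, in line with the 95% confidence intervals in Statistical analysis. The correlation r between the baseline covariate and 6-month OKS is not in the documents; 0.3, 0.5 and 0.7 are assumed.

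**Reproducing the planned size.** The normal approximation gives 2 × (1.960 + 0.842)² × 7.4² / 5² = 34.4, so 35 per arm, and 70 / 0.9 = 78. The t-test version gives 36 per arm, and 72 / 0.9 = 80, the stated figure. The plan is therefore sized for an unadjusted comparison with 36 analysed per arm (power 80.7%).

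**What adjustment does.** Including a covariate with correlation r reduces the residual SD to 7.4 × √(1 − r²), that is 7.06, 6.41 and 5.28 for the three values of r. By the normal formula with 36 per arm, power rises from 81.8% to 85.2%, 91.2% and 98.0%. The simulation below uses t-tests and gives slightly lower values.

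**Simulation.** 100,000 trials per setting, 36 per arm, one normally distributed baseline covariate, true difference 5. Site and age are not modelled. Each trigger is one possible meaning of imbalanced; the protocol chooses none. The share firing is the proportion of trials in which the covariate enters the model.

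| Rule | Share firing | Power, r = 0.3 | r = 0.5 | r = 0.7 |
|---|---|---|---|---|
| Never adjust | 0% | 80.7% | 80.8% | 80.6% |
| Adjust if baseline p < 0.05 | 5% | 81.0% | 81.7% | 82.5% |
| Adjust if p < 0.10 | 10% | 81.2% | 82.5% | 84.1% |
| Adjust if p < 0.20 | 20% | 81.5% | 83.7% | 86.7% |
| Adjust if standardised difference > 0.25 | 29% | 81.8% | 84.8% | 88.8% |
| Adjust if standardised difference > 0.10 | 67% | 82.9% | 87.8% | 94.3% |
| Always adjust | 100% | 83.6% | 90.0% | 97.5% |

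**Share of the available gain recovered** = (triggered − never) / (always − never). Example, r = 0.5 and standardised difference > 0.25: (84.75 − 80.77) / (89.95 − 80.77) = 3.98 / 9.18 = 43%. Across r = 0.3, 0.5 and 0.7 the shares are about 8%, 10% and 11% for p < 0.05; 36%, 43% and 49% for a standardised difference above 0.25; and 73%, 77% and 81% above 0.10.

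**Type I error**, same simulation with no true difference. Under each fixed trigger it is 2.7% to 4.7%. If the more favourable of the adjusted and unadjusted results could be reported, it is 6.3%, 7.3% and 8.4% for the three values of r.

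**The case against.** The other side has good points, and most of them limit the size of this one.

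- **Testing.** A reader might infer that baseline balance will be tested for significance. The text says only that comparability is assessed; the tests mentioned in that section concern model assumptions, and the baseline table is described as summaries. With no test, threshold or list of factors, it cannot be calculated how often some factor would count as imbalanced.
- **Importance.** The rule also requires importance, which may well mean prognostic strength, the right criterion. That stands, but it does not rescue a strong predictor that is balanced.
- **Primary model.** A reader might infer that the primary model will be picked after seeing the arms. A primary model is stated, and the rule is conditional and sits under a sensitivity heading. However, the sentence speaks of adjustment in the analysis without confining it to a sensitivity analysis, so the point is open either way.
- **Power.** A reader might infer that imbalance-triggered adjustment recovers almost none of the gain. That is true only of a 5% significance trigger. The rule does not reduce power compared with no adjustment; the shortfall comes from not naming baseline OKS, so deleting the rule alone would gain nothing.
- **SAP.** Covariate lists and definitions are usual SAP content, and the SAP is not shown. That answers the undefined terms. It does not answer the criterion itself: a SAP that follows this text would still use observed imbalance, which can be judged only once baseline data are seen by arm.

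**Conclusion.** The concern holds in this limited form: adjustment beyond site and age is tied to observed imbalance, which is the wrong criterion, and the primary OKS model omits baseline OKS. Always including it would raise power from about 81% to 84%, 90% or 98% at r = 0.3, 0.5 or 0.7. How much of that an imbalance rule recovers ranges from about a tenth to about four fifths, depending on a threshold that the protocol leaves undefined; none of the triggers examined recovers all of it. At r = 0.3 the whole gain is only about 3 points.

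The trial is not underpowered on this account, because its 80% does not rely on the adjustment. Nor does the document support a charge of inflated type I error: a fixed trigger stays at or below 5%, and the 6% to 8% figures need a freedom to report the better result that the protocol does not grant, though its wording does not expressly rule it out. All sizes rest on the assumed correlations, two-sided 5% significance, 36 analysed per arm and 7.4 as the SD of the 6-month score.

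**What to change.** Replace the imbalance-triggered rule. State that the primary OKS model includes baseline OKS, site and age group whatever the observed balance. For the other outcomes, include the baseline value of that outcome where it is collected. Keep the descriptive baseline table as already planned. Label any further adjustment prompted by observed imbalance as a sensitivity analysis that does not replace the primary estimate.

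The cost is wording in the protocol and SAP, settled before any comparison between the arms. It needs no additional participants, visits or measurements.
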